## Abstract

**Background:**

Perioperative anxiety is one of the main psychological stresses experienced by patients who undergo cancer surgery. The surgery itself inevitably causes a stress response characterized by activation of the sympathetic nervous system and the hypothalamic–pituitary–adrenal axis. Both the perioperative anxiety and surgical stress response lead to increased levels of catecholamines and prostaglandins, which may be related to perioperative suppression of antimetastatic immunity and tumor-promoting alterations in the microenvironment. Hence, we designed this clinical trial to investigate the effect of electroacupuncture in reducing perioperative anxiety and surgical stress response.

**Methods:**

This is a randomized, single-center, parallel, and controlled clinical trial. Seventy-eight participants between the ages of 35 and 85 with gastric or colorectal cancer who plan to undergo tumorectomy will be randomly divided into an electroacupuncture group and a control group. The primary outcome will be the six-item short form of the State-Trait Anxiety Inventory score. The secondary outcomes will be the Amsterdam Preoperative Anxiety and Information Scale score; levels of plasma cortisol, adrenocorticotropic hormone, interleukin-6, and tumor necrosis factor-α; first exhaust time after surgery; postoperative quality of the recovery-15 score, numeric rating scale for pain score; and dosage of postoperative analgesics.

**Discussion:**

Cumulative studies revealed the efficacy of various types of acupuncture therapy with regard to reducing the anxiety and stress response caused by surgery. We expect that the results of this trial will provide high-quality clinical evidence for the choice of perioperative acupuncture for patients undergoing cancer surgery.

**Clinical trial registration:**

https://www.chictr.org.cn, identifier ChiCTR200003 7127.

## Introduction

Psychological factors such as anxiety are prevalent in patients undergoing surgery (1, 2). They tend to affect postoperative recovery and increase the risk of postoperative complications, hospital stays, and even mortality (3, 4). In particular, patients with cancer are naturally subject to psychological stress caused by a cancer diagnosis and prolonged treatment, including perioperative anxiety, which may trigger endocrinological and immunological responses that affect not only the short-term recovery but also the cancer progression and long-term survival rates (5).

Perioperative anxiety, which is one of the main psychological stresses experienced by patients who undergo surgery, can cause activation of the sympathetic nervous system (SNS) and the hypothalamic–pituitary–adrenal (HPA) axis. This results in the consequent release of stress hormones, including catecholamines and glucocorticoids (6). Notably, the stress response caused by surgery can similarly lead to sympathetic nerve excitation and increased secretion of stress hormones (7). Among the hormonal and metabolic changes due to the patients’ anxiety and the tissue damage itself, the increased levels of catecholamines and prostaglandins are related to perioperative suppression of antimetastatic immunity and tumor-promoting alterations in the microenvironment, which have been highlighted as key deleterious mediators of surgery (5, 8).

Presently, enhanced recovery after surgery is recommended to minimize the surgical stress response and maintain homeostasis by application of multiple interventions, including shorting-acting anesthetic agents intraoperatively and non-opioid oral analgesia for postoperative pain management (9, 10). For perioperative anxiety, anxiolytic preanesthetic medications, such as benzodiazepines, opioids, and beta-blockers, are not strongly recommended due to the adverse side effects of these drugs (11, 12). Non-pharmacological methods such as preoperative visit (13), cognitive behavioral therapy (14), music therapy (15), and acupuncture therapy (16–18) have shown potential for the alleviation of patients’ preoperative anxiety.

Acupuncture therapy as a hallmark of traditional Chinese medicine has previously been used in the field of analgesia and pain management in China, and it is now usually applied perioperatively to patients undergoing surgery, beyond the scope of traditional anesthesia (19). Moreover, acupuncture therapy appeared to be an effective approach to reduce preoperative anxiety compared with placebo or non-treatment conditions (17). Furthermore, another study investigated the application of electroacupuncture (EA) to reduce surgical stress response and found a clear reduction in the levels of stress hormones from 30 min to 10 h postoperatively in addition to the reduced postoperative anxiety (20). Based on these findings, we hypothesized that EA can reduce perioperative anxiety and postoperative stress response. This study focuses on the effects of EA on perioperative anxiety and stress response in patients undergoing surgery for gastric or colorectal cancer. The aim of this study was to provide clinical evidence for acupuncture intervention in the alleviation of perioperative anxiety and stress response. We present the protocol for this study in accordance with the SPIRIT reporting checklist.

## Methods

### Study design

This study is a randomized, single-center, parallel, and controlled clinical trial in strict accordance with the Consolidated Standards of Reporting Trials (CONSORT) and Standards for Reporting Interventions in Clinical Trials of Acupuncture (STRICTA) guidelines (21–23). This study will be conducted to evaluate the effect of EA on perioperative anxiety and stress response in patients undergoing resection of gastric or colorectal cancer. The study will be conducted in Yueyang Hospital of Integrated Traditional Chinese and Western Medicine, affiliated to Shanghai University of Traditional Chinese Medicine. A total of 78 patients will be recruited and randomly divided 1:1 into an EA group and a control group. The study design is depicted in Figure 1 and the schedule of this trial is shown in Table 1.

**FIGURE 1 F1:**
[figure not shown]
The flowchart of the trial.

**TABLE 1 T1:** The study schedule for enrollment, treatments, outcome measurements, and data collection.

Timepoint	Study period							
	**Enrollment**	**Allocation**	**Post-allocation**					
	**Pre-2**	**0**	**Pre-1**	**Pod-0**	**Pod-1**	**Pod-2**	**Pod-3**	**Pod-7**
**Enrollment**								
Inclusion criteria	×							
Exclusion criteria	×							
Informed consent	×							
Randomization	×							
Allocation		×						
**Interventions**								
EA group			×	×	×	×	×	
Control group			×	×	×	×	×	
**Outcome measurement**								
STAI-S6		×	×	×	×		×	
Cort, IL-6, ACTH, TNF-α		×			×		×	
APAIS		×	×	×				
QoR-15					×		×	
First exhaust time					×	×	×	×
NRS		×			×		×	
Analgesic dosage					×	×	×	
Adverse events			×	×	×	×	×	×

According to SPIRIT 2013 statement: defining standard protocol items for clinical trials. Pre, preoperative day; Pod, postoperative day; STAI-S6, six-item short form of the State-Trait Anxiety Inventory; Cort, cortisol; ACTH, adrenocorticotropic hormone; IL-6, interleukin-6; TNF-α, tumor necrosis factor α; APAIS, Amsterdam Preoperative Anxiety and Information Scale; QoR-15, quality of recovery-15; NRS, numeric rating scale.

### Participants

This study will include 78 participants between the ages of 35 and 85 years of age with gastric or colorectal cancer who plan to undergo tumorectomy. Based on the inclusion criteria, potential participants are being identified by screening the admission records and surgery schedule of patients in the Department of Gastroenterology Surgery.

### Inclusion criteria

Participants who fulfill the following criteria will be included: (I) 35 to 85 years of age, (II) planning to undergo surgery for gastric or colorectal cancer, and (III) willing to participate in the study and provide signed informed consent forms. There was no restriction on the inclusion of participants based on sex.

### Exclusion criteria

The exclusion criteria are as follows: (I); requiring combined removal of other organs; (II) having previously undergone abdominal surgery and presence of obvious abdominal adhesions during surgery; (III) pregnant and lactating; (IV) having anxiety, depression, other mental diseases, or cognitive dysfunction; and (V) having contraindications to acupuncture, such as local skin infection at acupoints.

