### Interventions

After signing the informed consent forms, all the eligible participants will be randomized into one of the two groups (the EA group or the control group). Participants of the EA group will receive six sessions of EA starting from 1 day before the surgery to the third day after the surgery. On the day of surgery, the EA session will be performed 30 min before the surgery until the surgery ends; while on all other days, the EA session will be performed in the afternoon. All acupuncture sessions will be delivered by experienced acupuncturists according to the standard operating procedures at the acupoints as follows: DU23 (Shangxing), DU20 (Baihui), DU29 (Yintang), LI4 (Hegu), PC6 (Neiguan), LU9 (Taiyuan), ST36 (Zusanli), ST37 (Shangjuxu), and LR3 (Taichong), all of which are selected based on the previous systematic review and our clinical experience (17). Disposable sterile stainless steel acupuncture needles (40 mm in length and 0.25 mm in diameter) will be inserted at the acupoints to a depth of 10–20 mm, which will be determined by the acupuncturists according to the participants’ body type. De qi sensation will be obtained through rotating the needles, and then the needles on the DU23 (Shangxing), DU29 (Yintang), PC6 (Neiguan), and LU9 (Taiyuan) acupoints will be stimulated using the HANS acupoint nerve stimulator (HANS-200A; Nanjing Jisheng Medical Co) at a constant frequency of 2 Hz and an intensity of 5 mA for 30 min per session. Participants assigned to the control group will receive the same course of treatment as the EA group. However, the acupuncturists will withdraw the needles immediately without De qi sensation, and the EA device will be connected to the acupoints by insulating tapes without the current passing.

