### Primary outcome measures

The primary outcomes will measure changes in the STAI-S6 scores between the baseline and on the day of the surgery. The STAI-S6 will be used to assess the anxiety levels during the perioperative period. It is a standardized short form of the Spielberger STAI, in which the 40 questions of the Spielberger STAI have been reduced to three anxiety-present and three anxiety-absent questions (24, 25). Because of its simplicity, the STAI-S6 can be completed rapidly by participants, and it has been used to assess anxiety levels, including surgery-related anxiety levels, in many previous studies (16, 26).

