### Secondary outcome measures

Besides the primary outcome measurement, the STAI-S6 will be assessed 1 day before the surgery, 1 day after the surgery, and 3 days after the surgery as well, aiming to observe the anxiety levels during the perioperative period. Assessment for the each group at other time points except the baseline will be conducted following 30 min of the intervention.

The stress response will be evaluated by measurement of the levels of plasma cortisol (Cort), adrenocorticotropic hormone (ACTH), interleukin-6 (IL-6), and tumor necrosis factor-α (TNF-α). The stress response to surgery is characterized by activation of the HPA axis and the SNS, in which ACTH synthesized by the anterior pituitary and Cort secreted by the adrenal cortex are the two representative hormones that increase in response to a surgical stimulus (7). It is well established that IL-6 and TNF-α participate in the activation of the HPA axis and increase plasma concentrations of ACTH and Cort (27). The levels of both of these cytokines have been measured in previous studies to evaluate the intensity of surgery-related stress response (28, 29). The levels of plasma Cort, ACTH, IL-6, and TNF-α will be measured 1 day before the surgery and 1 and 3 days after the surgery. To avoid the influence of circadian fluctuation, the plasma samples will be obtained strictly at the same time in the morning.

The Amsterdam Preoperative Anxiety and Information Scale (APAIS) will be used to specifically assess the preoperative anxiety levels. This scale consists of four questions related to anxiety and has been proven to correlate well with the full version of the STAI (30). The Chinese version of the APAIS has a high degree of reliability and validity for the Chinese population in the evaluation of preoperative anxiety (31). The APAIS will be assessed at the baseline, 1 day before the surgery, and on the day of the surgery.

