### Statistical analysis

The statistical analysis of all data will be performed by two analytical researchers, independent of the trial. All the outcomes will be subjected to an Intent-to-Treat analysis based on the initial allocation. For missing data, the multiple imputation method will be applied. IBM SPSS Statistics (version 25.0) will be used for statistical analysis. All continuous variables conforming to normal distribution will be expressed as mean ± standard deviation, while those that do not conform to normal distribution will be expressed as median and quartile spacing. For enumerative variables, frequency and the corresponding percentage will be provided. To compare variables between the two groups, independent samples *t*-test for normally distributed data and the nonparametric Mann–Whitney *U* test for non-normally distributed data will be used. Different time point assessments will be analyzed using generalized estimating equation. Differences within groups will be assessed using the paired *t*-test for normally distributed data and the Wilcoxon signed-rank test for non-normally distributed data.

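### Exclusion criterion (II) turns on a finding made at the operation, after randomisation and the start of treatment, and cannot operate alongside the stated intention-to-treat analysis

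*Protocol article*

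**What the plan says.** Exclusion criterion (II) in the Protocol article (Exclusion criteria) reads "having previously undergone abdominal surgery and presence of obvious abdominal adhesions during surgery". It joins two conditions, and both must be met.

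Table 1 marks the inclusion criteria, exclusion criteria, consent and randomisation at Pre-2 only, and allocation in the next column. Interventions run from Pre-1 to Pod-3. The Interventions section agrees: "After signing the informed consent forms, all the eligible participants will be randomized into one of the two groups". It describes "six sessions of EA starting from 1 day before the surgery to the third day after the surgery", and for the operating day it says that "the EA session will be performed 30 min before the surgery until the surgery ends".

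The Statistical analysis section states: "All the outcomes will be subjected to an Intent-to-Treat analysis based on the initial allocation". Missing data are to be handled by multiple imputation.

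Nothing in the article says whether a patient whose adhesions are found at the operation stays in the analysis, is withdrawn or is replaced.

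**The concern.** An eligibility rule should use facts available before randomisation. This one appears to need a fact that does not exist until the abdomen is open. Anyone who meets it has by then been randomised, has had the session on the day before surgery and has begun the session on the operating day.

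The stress response is the trial's second aim (Discussion), and its postoperative markers are measured on days 1 and 3. QoR-15, pain, first exhaust time and analgesic dosage are also collected after surgery. Adhesions plausibly mark the longer and harder operations, so removing these patients selects on something related to those outcomes. No definition is given of how marked the adhesions must be, so the decision is a surgeon's judgement, made while the electroacupuncture or sham set-up may be in use in theatre.

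**Working it through.** **Step 1: order of events.**

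| Event | When | Source |
|---|---|---|
| Exclusion criteria checked, randomisation | Pre-2 | Table 1 |
| Allocation | Column 0, before Pre-1 | Table 1 |
| First session | Pre-1 | Table 1; Interventions |
| Operating-day session begins | 30 min before surgery | Interventions |
| Adhesions can be seen | During the operation | Exclusion criteria (II) |
| Stress markers, QoR-15, pain, first exhaust time, analgesic dosage | Pod-1 onwards | Table 1 |

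The adhesion finding comes after randomisation and after treatment has begun.

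**Step 2: the two ways to run the plan.**

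- *Apply the criterion.* Randomised, treated patients are removed, so the analysis is not by initial allocation for all outcomes.
- *Keep intention-to-treat.* Every randomised patient is analysed, so the operative half of the criterion does nothing.

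Multiple imputation does not settle the matter. It fills in values for patients who belong to the analysis set; it does not decide whether a patient later found ineligible belongs to it.

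**Step 3: where the primary endpoint falls.** The primary outcome is "changes in the STAI-S6 scores between the baseline and on the day of the surgery". On timing, the Secondary outcome measures section says: "Assessment for the each group at other time points except the baseline will be conducted following 30 min of the intervention". If this means after 30 min of stimulation, the score is taken at about the start of surgery, before adhesions are seen. If it means 30 min after the session ends, the score is taken after surgery and after the finding. Steps 1 and 2 hold under either reading.

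**Step 4: size.** First, the plan's own figure. With SD 4.04, difference 6.11 − 2.78 = 3.33 and the printed multipliers:

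n = 2 × (1.96 + 1.28)² × 4.04² / 3.33² = 30.9, so 31 per arm.

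31 / 0.8 = 38.75, so 39 per arm and 78 in total. The dropout allowance is 78 − 62 = 16. (The multiplier 1.28 belongs to 90% power, although the text says 80%. This explains the 0.90 in the first row below.)

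The documents give no rate for the criterion, so 5% to 20% is an assumption. Removal fraction x is taken on top of the full 20% dropout:

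n per arm = 39 × 0.8 × (1 − x); power = Φ(3.33 / (4.04 × √(2/n)) − 1.96)

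| x (assumed) | Removed of 78 | n per arm left | Power |
|---|---|---|---|
| 0 | 0 | 31.2 | 0.90 |
| 5% | 3.9 | 29.6 | 0.89 |
| 10% | 7.8 | 28.1 | 0.87 |
| 15% | 11.7 | 26.5 | 0.85 |
| 20% | 15.6 | 25.0 | 0.83 |

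Power stays above the stated 80% throughout, so loss of power is not the main harm.

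**The case against.** The strongest defence is that the protocol never says these patients are dropped, and that it does promise intention-to-treat. That is correct. A reader might infer a planned exclusion from the analysis, but the documents do not state one. What stands is that an exclusion criterion and an analysis rule cannot both take effect.

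A second defence reads criterion (II) as history: adhesions noted at the earlier operation. This would fit a single check at Pre-2. It is possible but strained, because in this protocol surgery ordinarily means the index operation. If it is what was meant, the wording should say so.

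Third, adhesions from earlier surgery exist before randomisation, and nothing in the documents suggests that a session or two could cause them. Excluding on such a feature, judged without knowledge of arm, narrows both arms alike and does not in itself bias the comparison. This stands: bias is a risk, not a demonstrated result. The risk remains because the judgement is undefined and made in theatre. Randomisation and blinding extends blinding to participants and to researchers other than the acupuncturists, but does not name the surgeons.

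Three further inferences should be resisted:

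- *That the finding always comes after the primary endpoint.* This depends on one reading of the assessment time (step 3).
- *That criterion (I), "requiring combined removal of other organs", has the same defect.* It can be read as a planned resection known at screening, particularly as candidates are identified from admission records and the surgery schedule.
- *That the trial would be underpowered.* The rate is assumed, criterion (II) needs both conditions, and the table shows power above 80% even at 20% removal.

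**Conclusion.** The point holds as an unreconciled contradiction. On the natural reading, criterion (II) can be met only after randomisation and after treatment has begun, and applying it is incompatible with the analysis by initial allocation that the protocol states. The sections must be reconciled.

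The consequence falls mainly on the postoperative stress, pain and recovery outcomes, where removal would select on operative difficulty. For anxiety measured before incision, the operative finding is irrelevant and exclusion would only discard valid data. If anxiety on the operating day is instead measured after surgery, the primary outcome is exposed to the same selection.

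The number of patients affected cannot be taken from the documents. The range of about 4 to 16 of 78 rests wholly on the assumed 5% to 20%. The conclusion does not depend on that rate.

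**What to change.** 1. Reword criterion (II) so that it uses only facts known before randomisation and keeps both conditions: prior abdominal surgery and adhesions already documented. Replacing the conjunction with an either/or would exclude everyone with prior abdominal surgery and shrink the pool in a trial whose recruitment has already been delayed.
2. State that patients found at the operation to have adhesions, or to need combined resection, stay in the intention-to-treat set for all outcomes. Because recruitment is described as under way, the statement should also cover patients already randomised.
3. Record the operative finding for every patient, and use it only in a sensitivity analysis of the postoperative stress, pain and recovery outcomes.

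These changes concern eligibility and the analysis set only; they take no position on clinical management after such a finding. The cost is a short eligibility amendment, one sentence in the analysis section and one recorded item. The planned total remains 78. The downside is slightly more variable recovery outcomes, because some harder operations stay in the comparison.

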### Sample size

According to the difference in the six-item short form of the State-Trait Anxiety Inventory (STAI-S6) scores between the two groups at the baseline and on the day of the surgery, the required sample size of each group will be calculated by the data statistician. Based on our previous pilot study, the difference in the standard deviation of STAI-S6 scores is 4.04 points. The STAI-S6 score changes 6.11 points in the EA group and 2.78 points in the control group. On the basis of a 5% false-positive error rate (α = 0.05, two-sided) and 80% power (β = 0.2), the sample size is estimated as follows:

$$\text{n}=\frac{2\,{\left({\text{Z}}_{\alpha /2}+{\text{Z}}_{\beta }\right)}^{2}\times \sigma^{2}}{{\left(\mu_{2}-\mu_{1}\right)}^{2}}=\frac{2\,{\left(1.96+1.28\right)}^{2}\times 4.04^{2}}{{\left(6.11-2.78\right)}^{2}}\approx 31$$

A sample size of at least 31 participants should be recruited in each group. Assuming a dropout rate of approximately 20%, a total of 78 participants will be enrolled in the trial.

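### The sample-size text states 80% power, but the formula uses the 90% quantile (1.28), so the stated power and the 31 per group do not match

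*Protocol article*

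**What the plan says.** The Sample size section bases the calculation on the STAI-S6 difference between baseline and the day of surgery, which is also the primary outcome. It gives these inputs:

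- error rate: "5% false-positive error rate (α = 0.05, two-sided";
- power: "80% power (β = 0.2), the sample size is estimated as follows";
- variability, from a pilot study: "the difference in the standard deviation of STAI-S6 scores is 4.04 points";
- effect, from the same pilot: "The STAI-S6 score changes 6.11 points in the EA group and 2.78 points in the control group".

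The displayed equation is the usual normal-approximation formula for two means. It substitutes 1.96 for Z_alpha/2 and 1.28 for Z_beta, and arrives at about 31. The text concludes: "A sample size of at least 31 participants should be recruited in each group". It then adds: "Assuming a dropout rate of approximately 20%, a total of 78 participants will be enrolled in the trial". The Study design section repeats the total and the 1:1 allocation: "A total of 78 patients will be recruited and randomly divided 1:1 into an EA group and a control group". No other section states a power or explains the 1.28.

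**The concern.** The sentence and the equation describe two different designs. A beta of 0.2 corresponds to a normal quantile of 0.84; 1.28 corresponds to a beta of 0.10. The stated power and the stated sample size therefore cannot both be right for these inputs.

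Power is a basic design figure. Anyone who recalculates the size from the stated power gets a smaller trial and cannot tell whether the power or the number of patients was intended. Anyone who reads the type II error from the text takes it to be 20% at the assumed effect, about twice what the calculation implies.

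The SD raises a second, smaller question. The formula needs the between-patient SD of the change score, because the effect is a difference in mean change. The wording used for 4.04 does not describe that quantity, so a reader cannot be sure that the right SD was entered.

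**Working it through.** **Inputs, all from the Sample size section**

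- Difference in mean change: 6.11 − 2.78 = 3.33
- SD: 4.04, taken as the common SD of the change, as the formula uses it
- Two-sided alpha 0.05, so Z_alpha/2 = 1.96
- Allocation 1:1; dropout 20%
- Standardised difference: 3.33 / 4.04 = 0.824

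**Formula:** n per group = 2 (Z_alpha/2 + Z_beta)² SD² / difference²

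**Step 1. Reproduce the printed figure (Z_beta = 1.28).**
2 × (1.96 + 1.28)² × 4.04² / 3.33² = 2 × 10.4976 × 16.3216 / 11.0889 = 30.90, so 31 per group.
Dropout: 31 / 0.8 = 38.75, so 39 per group and 78 in total. Both printed figures reproduce.

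**Step 2. Identify the power that 1.28 represents.**
The standard normal distribution function at 1.28 is 0.8997, that is, 90% power. The quantile for 80% is 0.842.

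**Step 3. Use the stated power (Z_beta = 0.84).**
2 × (1.96 + 0.84)² × 4.04² / 3.33² = 2 × 7.84 × 16.3216 / 11.0889 = 23.08, so 24 per group.
Dropout: 24 / 0.8 = 30 per group, 60 in total, which is 18 fewer than 78.

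**Step 4. Power at the relevant sizes, two-sided 5%.**

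| n per group | Normal approximation | Exact (noncentral t) |
|---|---|---|
| 24 | 81.5% | 79.8% |
| 25 | 83.0% | 81.5% |
| 31 | 90.1% | 89.1% |
| 32 | 90.9% | 90.1% |
| 39 | 95.4% | 94.9% |

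By the exact method, 80% power needs 25 per group (25 / 0.8 = 31.25, so 32 per group and 64 in total), and 90% power needs 32 per group.

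**Step 5. Could another convention give 31 at 80% power?**
A one-sided 5% test needs 19 per group for 80% power and 26 for 90%. Neither gives 31, and the text says two-sided in any case.

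**Step 6. What the SD wording could change.**
Suppose 4.04 were the SD of a single score, equal at both times. The SD of the change would then be 4.04 × √(2(1 − r)), where r is the correlation between baseline and day of surgery. The protocol gives no r, so the values below are assumptions. Exact power at 31 per group:

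| Assumed r | Power |
|---|---|
| 0 | about 62% |
| 0.3 | about 77% |
| 0.5 | 89% |
| 0.7 | about 98% |

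At r = 0.5 the two SDs are equal, so that row only repeats the base case. At r = 0.3 with all 39 per group, power is about 86%.

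**The case against.** The strongest reply is that the error does no harm to the trial. On the protocol's own assumptions, 31 per group gives more power than the text claims. The equation, the 31, the dropout allowance and the total of 78 all agree with one another, and only the stated power is out of line. No analysis or enrolment target depends on it. A null result should in any case be read from the estimate and its confidence interval, which do not depend on the planned power. All of this is fair and limits the consequence, but it does not make the stated power correct.

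On the SD, the context favours the intended meaning: the section speaks of baseline and day of surgery, the neighbouring figures are changes, and the formula uses 4.04 as the common SD. That 4.04 is a single-score SD is a possibility and is not shown by the document. The correlations in Step 6 are assumptions, and they show only why the wording should be made clear.

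Finally, the document does not reveal whether 80% or 1.28 was intended. That stands, and the sponsor should confirm it.

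A misprint or a text-extraction fault can be ruled out, because the printed 31 follows from 1.28 and not from 0.84.

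**Conclusion.** The concern holds. The stated 80% power does not belong to the stated 31 per group; the calculation as printed is for 90% power. At 80% the same inputs give 24 per group and 60 in total by the protocol's formula (25 and 64 by the exact t-test), against 31 and 78. At 31 evaluable per group the power is 90.1% by the formula and 89.1% exactly, about 10 points above the figure in the text. The mismatch is conservative, so the trial is not underpowered on its own assumptions. These results rest on a difference of 3.33 and on 4.04 being the SD of the change score. The second of these is the natural reading but is not what the text says. A wrong figure for a core design parameter must be corrected even though the size of the trial can stay as it is.

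**What to change.** Keep 31 evaluable patients per group and 78 in total. In the Sample size section:

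1. Restate the power as 90% (beta = 0.10, Z_beta = 1.28), after the sponsor has confirmed from its records that this was the intended value. It is the smallest repair, because 1.28, 31 and 78 already agree.
2. Add that the exact t-test power with 31 evaluable per group is about 89%.
3. Describe 4.04 as the between-patient SD of the baseline-to-day-of-surgery change in STAI-S6, if that is what the pilot gave. If it is not, recompute the power with the SD of the change.

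If the records show that 80% was intended, use 0.84 in the equation and give the resulting 24 per group, then state why 78 are nevertheless being enrolled.

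The cost is a sentence or so in one section. With 90% confirmed and 4.04 confirmed as the SD of the change, neither enrolment nor the analysis changes.
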